### Approvals and data safety and monitoring

The study was approved by the University of Michigan Institutional Review Board and the Research Review Committee of M-CARE. All data are obtained and managed by the UM pharmacy benefits manager, SXC Health Solutions, and by M-CARE, both of which require personal health information (PHI) in the course of their usual activities. To ensure protection of confidentiality, unique study identifiers are assigned to each patient and data are stripped of PHI prior to transmission to the evaluation team. Because the intervention constitutes a quality improvement initiative (taking place regardless of evaluation) and data are provided in limited datasets, informed consent requirements were waived. However, individuals were given the option to opt-out of the intervention at any time.

Because the intervention involved a benefit change, additional approvals were obtained from the three unions representing UM employees.

### Study design

The study employs an interrupted time series design, with medication adherence rates assessed at three-month intervals (unit of observation is the patient-quarter), beginning 30 months prior to the intervention (the 'pre' period) and continuing through the duration of the 30-month intervention (the 'post' period). This study design provides a strong test of the intervention's impact on medication adherence, separate from other ongoing temporal changes in adherence [34]. The advantage of this 'difference-in-difference' design is that any change in the control group values may reflect naturally occurring changes over time (perhaps due to policy or medical care changes), while any change in the UM intervention group values will reflect both the same naturally occurring trends, as well as the impact of the value-based co-payment reductions.

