### Study population identification

The initial intervention population included 2,507 UM employees and dependents enrolled in UM's pharmacy benefits plan and identified as individuals with diabetes based on at least one pharmacy claim for a diabetic hypoglycemic medication (oral, injectable, or inhaled) within the 12 months prior to intervention.

The initial control population included 8,637 M-CARE enrollees receiving coverage through other employers and identified as individuals with diabetes using the same pharmacy claims criteria. Figure 1 depicts the intervention and control groups and their relationship to the University and M-CARE.

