**Figure 1 F1:**
[figure not shown]
**Identification of intervention and control groups**. The large circle on the left (labeled 'U of M') depicts University of Michigan employees and dependants. The large circle on the right (labeled M-CARE) depicts M-CARE enrollees, with the central area of overlap representing UM employees enrolled in M-CARE. The subset of individuals with diabetes is depicted by the shaded circle labeled 'Diabetes.' The intervention group includes UM employees and dependents with at least one pharmacy claim for a glycemic medication (oral, injectable, or inhaled) within the 12 months prior to the study timeframe. The control group consists of M-CARE enrollees who are employees and dependents of other, non-UM employers with at least one pharmacy claim for a glycemic medication within the 12 months prior to the study timeframe.

While UM employee turnover is low, the population eligible for the intervention is not static. Both new UM employees with pre-existing diabetes and current employees newly diagnosed with diabetes are automatically enrolled in the intervention upon having an eligible pharmaceutical claim filed. The automatic enrollment design was chosen to reduce the burden of action required for individuals to benefit from the co-payment reductions. Participants could choose to opt-out of the program at any time. Further, UM employees and dependents not identified from pharmacy claims can opt-in to the program by contacting the Focus on Diabetes program coordinator and self-identifying that they have diabetes. While eligible for the full intervention, these 'opt-in' individuals will be excluded from analyses because there is no comparable control group.

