### Statistical analyses

#### Medication utilization (or uptake)

We classify an individual as utilizing therapy if any of their dispensed medications include a drug within the drug class of interest, either alone or in combination with another drug during each of the two one year windows in the pre-period and two one-year windows in the post-period. For analysis purposes, ACE-Inhibitors and ARBs are considered one drug class.

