#### Health care expenditures

To implement the 'difference in difference' approach to examining health care costs, we will use the same multiple time-series regression approach specified above. Initial cost models will use ordinary least squares with a log transformation of costs to account for the skewness of the distribution of health care expenditures. We will test two-part econometric models against the one-part model because the unit of analysis is the patient quarter, and there may be several individuals with no spending in any given quarter. The first part model will be a logit/probit modeling the probability of non-zero expenditure, and the second part will model expenditure conditional on non-zero spending [41].

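### Time before first diabetes treatment enters the baseline for cost and non-glycemic uptake, and it cancels between groups only if their newly treated shares are equal

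*Protocol article*

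**What the plan says.** - **Who is included.** Study population identification requires, for the intervention group, "at least one pharmacy claim for a diabetic hypoglycemic medication (oral, injectable, or inhaled) within the 12 months prior to intervention". Controls are "identified as individuals with diabetes using the same pharmacy claims criteria".
- **How far back the data go.** Study design sets ten pre-quarters, "beginning 30 months prior to the intervention", and ten post-quarters. Health care expenditures states that for costs "we will use the same multiple time-series regression approach specified above", with the patient-quarter as unit.
- **Uptake.** Primary outcomes and Medication utilization (or uptake) count a patient as a user if there is at least one fill in the class "during each of the two one year windows in the pre-period", and likewise in two post-years. Uptake therefore looks back 24 months, not 30.
- **Adjustment.** Model covariates lists age, gender, comorbidity, member status and number of medications. None records when diabetes treatment began.
- **A second anchor.** The Figure 1 legend places the qualifying claim "within the 12 months prior to the study timeframe", whereas the Methods text says "within the 12 months prior to intervention".

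**The concern.** A claim in months −12 to 0 shows treated diabetes in that year only. Nothing in the Methods text requires a claim at or before month −30. Someone first treated in spring 2006 therefore contributes about two years of earlier quarters, and one complete earlier uptake window, without treated diabetes. In the initial cohort everyone has been treated by 1 July 2006, so untreated time shrinks through the pre-period and is zero afterwards.

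If patients use more statins and ACE/ARBs and cost more once treated, each group's series climbs to the start date and then levels off. A segmented model with its break at that date reads the flattening as a change. Cost is the outcome most exposed, because Hypothesis 2 concerns cost growth and the model estimates a change in slope. Non-glycemic uptake is exposed through the earlier of its two pre-windows.

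What matters for the trial is whether this differs between groups. The comparison is not randomized, and the Discussion's own condition for controlling temporal trends is that they do not arise in one group alone at the moment the intervention starts. A break created by selection falls exactly at that moment, and its size depends on each group's newly treated share.

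**Working it through.** **The plan's own benchmark.** Statistical power gives 2,131 and 4,000 patients, 50% initial uptake, a 3.8-point change, 80% power and a 0.05 level (taken as two-sided).

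- Pooled proportion = (2,131 × 0.538 + 4,000 × 0.500) / 6,131 = 0.5132.
- Standard error under no difference = √[0.5132 × 0.4868 × (1/2,131 + 1/4,000)] = 0.01340; under the alternative it is 0.01338.
- Power = Φ[(0.038 − 1.96 × 0.01340) / 0.01338] = Φ(0.876) = 81%.

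The stated figure reproduces, so 3.8 points is a fair yardstick.

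**Assumptions, none of which the article gives.** Patients in the cohort were first treated at a steady yearly share *s*: 6% in one group, and 8–10% (cost) or 8–12% (uptake) in the other. Cost is *R* = 1.5 to 3 times higher once treated. Use of a non-glycemic class is *J* = 20 to 30 points higher once treated. The true effect is zero.

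**Cost slope.** At *t* years before July 2006 the untreated share is *u* = *s* × *t*; afterwards it is 0. With untreated cost set to 1, mean cost is *R* − *u*(*R* − 1). The between-group log difference is computed at quarter midpoints, from 2.375 to 0.125 years before the start.

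- *R* = 1.5, 8% against 6%. First quarter: ln(1.40500/1.42875) = −0.0168. Last pre-quarter: ln(1.49500/1.49625) = −0.0008. Pre-period slope ≈ 0.0159/2.25 = 0.0071 per year. Post-period slope is 0, so the slope change is −0.71% per year.
- *R* = 3, 10% against 6%. First quarter: ln(2.525/2.715) = −0.0726. Last pre-quarter: ln(2.975/2.985) = −0.0034. Slope ≈ 0.0692/2.25 = 0.0308. The segmented regression on all 20 quarters gives a slope change of −3.07% per year.
- Shares exchanged: +0.71 and +3.07% per year.
- Shares equal: 0.

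The article plans least squares on log patient-quarter costs. The mean of logs then differs by (*s*₁ − *s*₂) × *t* × ln *R*, so the slope change is 0.02 × ln 1.5 = 0.8% to 0.04 × ln 3 = 4.4% per year in absolute value. The 0.7 to 3.1% range is not exaggerated by working with the log of the mean.

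**Any-fill uptake.** Every cohort member has a hypoglycemic claim in the last pre-year. If use rises at first treatment, a fill later in that window already counts, so that window is essentially unaffected. In the window 12–24 months before the start, only patients first treated in the final year are untreated throughout; their share is *s* × 1. Averaging two pre-windows, the bias is *J* × (*s*₁ − *s*₂)/2.

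- 20 points × (0.08 − 0.06)/2 = 0.2 points.
- 30 points × (0.12 − 0.06)/2 = 0.9 points.
- If use starts some time after the first hypoglycemic claim, so that the last window carries half the deficit, the factor is 0.75 instead of 0.5: 0.3 to 1.35 points.
- Exchanged shares reverse the sign; equal shares give 0.

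**The case against.** The strongest reply is that a shared artefact is what the control group is there to remove. Both groups are selected by the same rule and the analysis is a difference-in-difference, so with equal newly treated shares, and an equal jump in use or cost at first treatment, every term cancels exactly. That stands.

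A reader might infer that the design builds in a break favouring Hypothesis 2, because the intervention group is younger (45.1 against 47.5 years) and uses fewer ACE/ARBs (43.4% against 48.7%). The documents do not support this. Table 2 also shows near-equal statin use (44.7% and 44.5%), metformin use (53.9% and 53.6%) and Charlson scores (1.43 and 1.46). No section gives a newly treated share, so the direction is unknown.

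The cohort definition is also unsettled. If the study timeframe in the Figure 1 legend includes the 30-month look-back, no untreated time enters at all. Conversely, Study population identification describes automatic entry of newly diagnosed university employees after the start, and Sample characteristics counts the 2,507 over the first year although the Methods call them the initial population. If later entrants are analysed with their earlier time, untreated time in the intervention group also falls after July 2006. These points limit what can be claimed about size, but they strengthen the case for stating one rule.

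Finally, an article may leave patient-quarter eligibility to a fuller document. The point here is narrower: the identification and look-back periods that the article does fix do not match.

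**Conclusion.** The point holds in conditional form. As the Methods text reads, patients first treated late in the pre-period put untreated time into the baseline of both groups, and the initial cohort has none after 1 July 2006. The planned contrast is unbiased from this source only under equal newly treated shares and equal jumps at first treatment, which the article neither reports nor adjusts for.

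Under the assumed shares, the possible bias is about 0.7 to 3.1% per year in relative cost growth and about 0.2 to 0.9 points in any-fill uptake, in either direction, and zero if the shares are equal. The uptake figure is at most about a quarter of the detectable 3.8 points (0.9/3.8 = 24%), so the main exposure is the cost slope. Adherence among users is not the target of this point. An actual bias, or one in favour of the intervention, is not shown.

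**What to change.** 1. Reconcile the Methods text with the Figure 1 legend on the identification window, and state one cohort rule, including the handling of later entrants, that applies to both groups.
2. Report, by group, the share of patients whose first observed hypoglycemic claim falls in each pre-period year. This tests the equal-share condition directly.
3. For cost, health care utilization and non-glycemic uptake, repeat the analyses in both groups among patients who already have a hypoglycemic claim in the first 12 months of the 30-month pre-period. As an alternative or in addition, use only patient-quarters and windows from each patient's first observed hypoglycemic claim onward.

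The cost is analysis wording and programming, since the article already provides for obtaining the claims. Some pre-period quarters are lost, the check cohort is smaller, and precision is slightly lower.

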## Procedures

### Intervention

#### Educational letter

One month prior to the co-payment reductions, an educational letter was sent out, with information on the general health benefits of medication adherence and the specific benefits of ACE/ARBs, statins, and tight glycemic and blood pressure control in diabetes. A phone number for a nurse case manager was provided for questions. A brief description of the impending co-payment reductions was provided, as well as a statement allowing individuals to opt-out of the study. A parallel educational letter was sent to the control group, differing from the UM letter only in exclusion of information about the co-payment reductions. The control group was also provided with a phone number for a nurse case manager available for questions [35,36].

#### Co-payment reductions

While the intervention was designed to reduce financial barriers to effective therapies, it was not meant to preclude the concomitant use of other incentive structures already in place. When the intervention went into effect, UM had a three-tiered formulary with co-pays of $7, $14, and $24 for generic (tier one), preferred brand (tier two), and non-preferred brand (tier three) medications, respectively. This underlying benefit structure was left intact with the value-based benefit laid on top. To maintain the underlying incentives to use lower cost drugs within a class, the intervention lowered co-pays in a graded fashion (tier one co-pays decreased by 100%, tier two by 50% and tier three by 25%) to a new three-tiered benefit structure of $0, $7, and $18 co-payments, respectively.

#### Data collection

Pharmacy claims were obtained for the intervention group from SXC Health Solutions, and for the control group from CatalystRx. Non-pharmacy claims were obtained from M-CARE for both groups. All data were transferred to the M-CARE claims administration office, which assigned unique study identifiers, managed the linkage of patient data across data sources and over time, and stripped the data of PHI prior to transfer to the evaluation team.

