**Methods:**

The FOD trial includes 2,507 employees and dependents with diabetes insured by one large employer. Approximately 81% are enrolled in a single independent-practice association model health maintenance organization. The control group includes 8,637 patients with diabetes covered by other employers and enrolled in the same managed care organization. Both groups received written materials about the importance of adherence to secondary prevention therapies, while only the intervention group received targeted co-payment reductions for glycemic agents, antihypertensives, lipid-lowering agents, antidepressants, and diabetic eye exams. Primary outcomes include medication uptake and adherence. Secondary outcomes include health care utilization and expenditures. An interrupted time series, control group design will allow rigorous assessment of the intervention's impact, while controlling for unrelated temporal trends. Individual patient-level baseline data are presented.

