### Study setting

The University of Michigan is a large Midwestern university with an enrollment of nearly 50,000 students. The university contracts with a single pharmacy benefits manager (PBM), SXC Health Solutions, for all of its employees, dependents, and retirees. Retirees were excluded from this study, however, because Medicare Part D and the FOD intervention were implemented in close proximity, making it difficult to isolate the effects of each from the other. The approximately 70,000 active UM employees and dependents are enrolled in several different health plans. The most frequently chosen plan is M-CARE, which, in 2006, enrolled approximately 81% of active UM employees and dependents.

M-CARE is a UM-owned non-profit independent-practice association model health maintenance organization (HMO) with approximately 200,000 enrollees throughout Southeastern Michigan in 2006. While UM enrollees use the university-contracted PBM (SXC Health Solutions), all other M-CARE enrollees receive pharmacy services through CatalystRx, the M-CARE-contracted PBM at the time the FOD intervention was initiated. Both SXC and CatalystRx use the same claims processing platform, allowing for acquisition of comparable data for both the intervention and control groups in this study.

M-CARE has a diabetes disease management program designed to improve patient adherence to recommended diabetes care processes. Therefore, any measured effect of targeted co-payment reductions is actually the incremental additional effect beyond the impact of the disease management program.

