##### Model covariates

To ensure findings are due to the co-payment reductions and not to underlying differences between the two groups, models will adjust for age, gender, comorbidity, member status (employee, spouse or dependent), and number of medications taken. Comorbidity is assessed using the Deyo modification to the Charlson comorbidity index [40], a well-validated measure of the burden of comorbid illness that was developed specifically for use with claims data.

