#### Subgroup analyses

Because depression is associated with worse adherence and higher costs in individuals with diabetes [12-15], subgroup analyses will be performed to explore for a differential effect of the intervention in those with depression. In turn, because there may be important differences between UM employees who enroll in M-CARE and those who enroll in other health plans, analyses will be repeated with and without the small subset enrolled in other health plans.

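### About 19% of the intervention group, and no controls, have no stated source of non-pharmacy claims, so analyses that include them cannot validly be run for utilisation, non-pharmacy or total cost, or Charlson-adjusted models

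*Protocol article*

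**What the plan says.** **Sources.** The Data collection section of the protocol article states: "Pharmacy claims were obtained for the intervention group from SXC Health Solutions, and for the control group from CatalystRx". It continues: "Non-pharmacy claims were obtained from M-CARE for both groups". No other source of medical claims is named.

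**Groups.** Under Study population identification: "The initial intervention population included 2,507 UM employees and dependents enrolled in UM's pharmacy benefits plan". Membership of M-CARE is not a condition. The 8,637 controls, by contrast, are M-CARE enrollees by definition. The Abstract says of the trial group: "Approximately 81% are enrolled in a single independent-practice association model health maintenance organization". The Study setting section gives the same share for the whole active workforce: M-CARE in 2006 "enrolled approximately 81% of active UM employees and dependents".

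**Analyses.** Under Subgroup analyses, "analyses will be repeated with and without the small subset enrolled in other health plans". The reason given is that employees who choose different plans may differ. Under Model covariates, the models adjust for comorbidity: "Comorbidity is assessed using the Deyo modification to the Charlson comorbidity index". Secondary outcomes are counts of visits, emergency use and admissions, together with pharmaceutical and non-pharmaceutical spending. Hypothesis 2 predicts slower non-pharmaceutical cost growth in the intervention group.

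**Related statements.** Table 2 heads the intervention column with 2,507 and reports a Charlson score of 1.43 (SD 0.65) without a separate denominator. The Study setting section describes any measured effect as additional to that of M-CARE's own disease management program.

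**The concern.** The stated data source and the stated analysis set do not fit together. Members of other health plans are in the intervention group through their pharmacy benefit, but nothing in the article provides their medical claims. The gap lies in one group only, so it does not cancel in a comparison with the controls.

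It affects every secondary outcome except pharmacy spending. It also reaches the primary outcomes in two ways: through the Charlson covariate and through the hospital-stay rule in the medication possession ratio (MPR). The planned repeat with and without the subset treats the matter as one of patient differences. It does not recognise that the data are absent, and it does not say which run governs the conclusion.

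**Working it through.** **1. The plan's own figure.** The article's only computed design figure is 80% power with 2,131 against 4,000 patients. A two-sided 5% comparison of two proportions gives power of 0.81 for uptake (50% against 53.8%) and 0.79 for MPR (65% against 68.5%). The figure is reproduced. It covers outcomes built on pharmacy claims, and the article gives no such figure for cost. It is used under the fix to price a smaller sample.

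**2. Size of the gap.**
- Share outside M-CARE: 100% − 81% = 19%.
- Intervention patients outside M-CARE: 0.19 × 2,507 ≈ 476.
- Intervention patients in M-CARE: 0.81 × 2,507 ≈ 2,031.
- Controls outside M-CARE: 0 of 8,637.
- The 81% is approximate. Each percentage point is 0.01 × 2,507 ≈ 25 patients.

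**3. What these members do and do not have.**

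| Item | Claims needed | Stated source for other-plan members |
|---|---|---|
| Uptake (any fill) | Pharmacy | Yes, SXC |
| Pharmacy spending | Pharmacy | Yes, SXC |
| MPR | Pharmacy, plus hospital dates for the in-hospital rule | Only in part |
| Visits, emergency use, admissions | Medical | None |
| Non-pharmacy spending | Medical | None |
| Total spending | Both | Pharmacy part only |
| Charlson score | Medical | None |

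**4. Were absent claims scored as zero in Table 2?** Suppose 19% had a Charlson score of 0. The M-CARE mean would then be 1.43 / 0.81 = 1.77. The variance between the two parts alone would be 0.81 × 0.19 × 1.77² = 0.48. The total variance reported is 0.65² = 0.42. A component cannot exceed the total, so 19% were not scored zero. This does not exclude a floor of 1 for diabetes alone: the M-CARE mean would be (1.43 − 0.19) / 0.81 = 1.53 and the between-part variance 0.81 × 0.19 × 0.53² = 0.04. Nor does it exclude a reduced denominator.

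**5. What zero-coding of costs would do.** The article gives no cost figures. Assume a baseline non-pharmacy cost B = $1,000, equal true growth g in both groups, no treatment effect and a constant 19% share at zero.
- *Absolute dollars:* 0.81Bg − Bg = −0.19Bg. For g of 5%, 10% and 20% this is −$9.5, −$19 and −$38, always 19% of control growth.
- *Log(cost + 1):* −0.19 × ln[(B(1+g)+1)/(B+1)], which is about −0.009, −0.018 and −0.035.
- *Ratio of means:* 0.81B(1+g) / 0.81B = 1 + g in both groups, so the bias is 0.
- *Second part of a two-part model of non-pharmacy cost:* the zeros drop out, so the bias is 0.
- *Set to missing, or excluded:* the bias is 0.

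**6. Total cost.** These members have pharmacy spending, so they would remain in a model of non-zero total cost with an understated amount. As an illustration, assume pharmacy cost of $600 growing 10% and non-pharmacy cost of $1,400 growing 5%.
- *Full data:* growth is 60 + 70 = $130 on $2,000, or 6.5%.
- *With 81% of non-pharmacy cost seen:* growth is 60 + 56.7 = $116.7 on $1,734, or 6.7%.

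Absolute growth is understated, while relative growth is slightly overstated. The direction depends on the scale.

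**The case against.** A reader might infer that the cost comparison is biased by 19% toward Hypothesis 2, or that these members have no cost data at all. The documents support neither.

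- **Coding.** Nothing in the article codes absent claims as zero. The remark about quarters without spending only motivates a two-part model. The team can identify the members concerned, since it plans runs with and without them. Step 4 shows that zero was not used for 19% of Charlson scores. This stands, although Table 2 says nothing about how costs are handled.
- **Scale.** Hypothesis 2 concerns a rate of growth, and the Health care expenditures section starts from logged costs. The 19% shortfall belongs to absolute dollars. This stands.
- **Pharmacy data.** SXC serves all university members, so fills and pharmacy spending exist for everyone. This stands.
- **Remedy already planned.** The run without the subset is the like-for-like M-CARE comparison. This stands in part. The run exists, but only as one of a pair that is justified by patient differences, and it is not made primary.
- **Detail left elsewhere.** A condensed article may leave coding and analysis sets to a fuller plan. That is fair for coding rules. It does not cover the mismatch, because the article itself states both the single source of medical claims and a run that needs claims from outside it.

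**Conclusion.** The point holds as a mismatch between data source and analysis set. About 476 of 2,507 intervention patients, and no controls, lack a stated source of medical claims. For utilisation, non-pharmacy and total spending, and Charlson-adjusted models, the run that includes them cannot validly be done from the sources named. Their MPR cannot be corrected for hospital days.

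A bias toward Hypothesis 2 is conditional. It needs zero-coding of absent costs, and it reaches 19% only for absolute growth. It vanishes under the three conditions in step 5: missing data, a ratio of means, or the second part of a two-part model of non-pharmacy cost. Total cost would be understated for these members because only their pharmacy spending is seen.

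The size rests on three assumptions: that the approximate 81% applies to patients with diabetes, that no unlisted source supplies the other plans' claims, and that the M-CARE share is stable. The share is given for 2006 only, and the article says that the eligible population is not static.

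**What to change.** - Make M-CARE enrollees in both groups (about 2,031 intervention patients) the primary analysis set for utilisation, non-pharmacy and total spending, and all Charlson-adjusted models; or name a claims source for the other plans.
- State that person-time without a medical claims feed is missing, never zero.
- Limit the run that includes other-plan members to outcomes that need pharmacy claims only, in models without Charlson. An MPR in that run would have to omit the hospital-day rule in both groups.
- Report the denominator of the Charlson score in Table 2.
- Limit the statement that the effect is additional to M-CARE's disease management program to M-CARE members.

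The cost is wording, a smaller intervention sample in these models, and conclusions confined to M-CARE members. By the method of step 1 with 8,637 controls, going from 2,507 to 2,031 raises the difference detectable with 80% power from 3.2 to 3.5 points for uptake and from 3.0 to 3.3 points for MPR. Both remain within the 3.8 and 3.5 points stated in the article. These figures ignore the repeated quarterly measurements.
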